## Abstract

**Introduction:**

Cancer-related fatigue (CRF) is one of the most common and debilitating side effects experienced by patients with breast cancer (BC) during postoperative chemotherapy. Family-involvement combined aerobic and resistance exercise has been introduced as a promising non-pharmacological intervention for CRF symptom relief and improving patients’ muscle strength, exercise completion, family intimacy and adaptability and quality of life. However, evidence for the practice of home participation in combined aerobic and resistance exercise for the management of CRF in patients with BC is lacking.

**Methods and analysis:**

We present a protocol for a quasi-randomised controlled trial involving an 8-week intervention. Seventy patients with BC will be recruited from a tertiary care centre in China. Participants from the first oncology department will be assigned to the family-involvement combined aerobic and resistance exercise group (n=28), while participants from the second oncology department will be assigned to the control group that will receive standard exercise guidance (n=28). The primary outcome will be the Piper Fatigue Scale-Revised (R-PFS) score. The secondary outcomes will include muscle strength, exercise completion, family intimacy and adaptability and quality of life, which will be evaluated by the stand-up and sit-down chair test, grip test, exercise completion rate, Family Adaptability and Cohesion Scale, Second Edition-Chinese Version (FACESⅡ-CV) and Functional Assessment of Cancer Therapy -Breast (FACT-B) scale. Analysis of covariance will be applied for comparisons between groups, and paired t-tests will be used for comparison of data before and after exercise within a group.

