### Sample size

According to a previous study,^24^ the score for CRF is expected to decrease by 2.29 points. According to the two-sided sample size test formula, a two-sided test with alpha=0.05 and 90% power will require a total sample of 23 patients in each of the two groups. To account for a 20% attrition rate, the required sample size is 56.

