### Study design

To avoid contamination among the research participants, this study will adopt a lottery method to randomly divide the hospital’s first and second oncology departments into a control group and intervention group and then select 28 patients from each ward who meet the requirements after screening by the inclusion and exclusion criteria.

The intervention team will consist of a sports rehabilitator, a senior clinical nursing specialist, a head nurse, three responsible nurses and a nursing graduate student. The sports rehabilitator will participate in the formulation of the exercise programme. The nursing specialist will participate in the guidance of the experimental programme. The head nurse and three nurses will be responsible for quality control, identifying problems in the implementation of the programme, and making rectifications. The graduate student will be responsible for explaining the intervention to the patients with BC and their families as well as data collection and collation. Group members will jointly develop an exercise instruction manual (including exercise form, methods, precautions, etc) and record an instructional video for the exercise protocol.

The researcher will explain the purpose and implementation process of the study to the patients with BC when they are admitted to the hospital for their first chemotherapy treatment (T0). After their agreement to participate, participants will be asked to provide written informed consent. The participants will be informed that they can withdraw from the study at any time without any consequences. After obtaining informed consent from the patients, the researcher will conduct the stand-up and sit-down chair test and grip test with patients and issue general information questionnaires along with the R-PFS, FACESⅡ-CV, and FACT-B. The intervention study will begin after the patients (and their family members) have completed their first assessment.

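### The abstract recruits 70 patients, but its own two groups and the Methods all total 56, and the other 14 are not explained

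*Protocol article*

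**What the plan says.** Four places in the protocol article bear on the number of patients.

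- Abstract, Methods and analysis, on the total: "Seventy patients with BC will be recruited from a tertiary care centre in China".
- The next sentence of the abstract, on the groups: "family-involvement combined aerobic and resistance exercise group (n=28") and "control group that will receive standard exercise guidance (n=28").
- Sample size: 23 patients per group are needed for a two-sided test at alpha 0.05 with 90% power, where "the score for CRF is expected to decrease by 2.29 points". The section then concludes: "To account for a 20% attrition rate, the required sample size is 56".
- Study design: the team will "select 28 patients from each ward who meet the requirements after screening by the inclusion and exclusion criteria".

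The figure of seventy appears once, in the abstract. The text describes no third group, reserve list, replacement rule or number to be screened.

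**The concern.** Two consecutive sentences of the abstract give totals that differ by 14. A reader who has only the abstract cannot tell whether the trial enrols 56 or 70, and a final report could be judged against either. The target should be unambiguous before enrolment ends, particularly here, because the Discussion says that participants and investigators cannot be blinded.

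Checking the 56 raises a second, much smaller question: whether it leaves the 23 patients per group that the plan requires once the plan's own 20% attrition has occurred.

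**Working it through.** **Inputs.** From the abstract: 70 recruited, 28 and 28 allocated. From Sample size: 23 per group, 90% power, two-sided alpha 0.05, a difference of 2.29 points, 20% attrition, total 56. From Study design: 28 per ward, two wards.

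**Step 1. Compare the totals.**

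| Place | Statement | Total |
|---|---|---|
| Abstract, recruitment sentence | seventy | 70 |
| Abstract, allocation sentence | 28 + 28 | 56 |
| Sample size | 56 | 56 |
| Study design | 2 × 28 | 56 |

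The gap is 70 − 56 = 14, so 70 is 25% above 56 (14/56). The 56 already contains the attrition allowance, so the allowance as stated does not account for the gap.

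**Step 2. Reproduce the 56.** Multiplying by one plus the attrition rate gives 23 × 1.2 = 27.6, rounded up to 28 per group, and 2 × 28 = 56. This matches the stated figure exactly.

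**Step 3. Check the 56 against 20% attrition.**

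- Expected to remain per group: 28 × (1 − 0.20) = 22.4, below 23.
- Number needed so that 23 remain: 23 / (1 − 0.20) = 28.75, rounded up to 29 per group, 58 in total.
- Attrition that 28 per group can absorb: 1 − 23/28 = 5/28 = 17.9%.

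**Step 4. Size of the effect on power.** The article gives no standard deviation, so the 23 cannot be derived directly. The SD has to be back-solved as an assumption from 23 per group, a difference of 2.29 and 90% power. The normal-approximation formula is SD = 2.29 / [(1.960 + 1.282) × √(2/23)] = 2.396. The t test gives 2.343. Keeping to one method throughout each row:

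| Method | Implied SD | Power at 23 per group | Power at 22 per group | Power at 22.4 per group (interpolated) |
|---|---|---|---|---|
| Normal approximation | 2.396 | 90.0% | 88.7% | 89.2% |
| t test | 2.343 | 90.0% | 88.6% | 89.2% |

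The loss is 1.3 to 1.4 points at 22 per group and 0.8 points at the expected 22.4.

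**The case against.** The strongest reply is that the operative text is consistent. Sample size, Study design and the abstract's own group sizes all lead to 56, and seventy is a single figure in an abstract. That stands. A reader might infer that the trial has no usable recruitment target, but the documents do not support this: anyone following the Methods would stop at 56.

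A second reply is that 70 could be the number approached or screened, since Study design takes 28 per ward after screening. This is possible, so it should not be stated as fact that 14 enrolled patients have no group. But the abstract says recruited, and the text gives no number screened. The flow chart (Figure 1) was not available for this check and should be looked at. Even if it explains the 70, the abstract should say so. Condensing a longer protocol does not account for a conflict between adjacent sentences.

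A third reply is that the attrition point is trivial. That largely stands: it amounts to one patient per group after rounding, and it would not merit a finding alone. It belongs here only because whoever corrects the total has to settle on one number.

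Two further inferences should be resisted.

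- Because 56/0.8 = 70 exactly, a reader might conclude that attrition was applied twice. Nothing in the article says so, and the match may be coincidence.
- A reader might put power at 22 per group as low as 87%. That figure comes from using the SD from the normal approximation (2.396) in a t test, which already gives only 88.7% at 23 per group. It is therefore not a fall from 90%.

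**Conclusion.** The point holds. The abstract's 70 contradicts the 56 given by its own groups, the Sample size section and the Study design section, a difference of 14 that the text does not explain. This follows from the stated figures alone, with no assumption. It needs correcting because enrolment and the final report depend on the figure, but the error is confined to one sentence of the abstract.

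The attrition arithmetic is a minor companion error. At 20% loss, 28 per group falls short of 23 by 0.6 of a patient, and power falls by about 1 point. The shortfall follows from the stated figures. The power figure depends on the back-solved SD of about 2.34–2.40, and on the 23 per group having been calculated for a simple two-group comparison of means. The 90% power claim is not seriously threatened on this account.

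**What to change.** 1. State one enrolment target in the abstract, Sample size and Study design. The Methods support 56, so replace Seventy with 56 in the abstract. If 70 is meant as something else, such as the number approached, say so there and keep 56 as the number enrolled.
2. Make the attrition statement agree with the target. Either keep 56 and say that 28 per group tolerates about 17.9% attrition (5 of 28) with 23 remaining, or keep 20% and state 58 (29 per department), changing the group sizes in the abstract and Study design to match.
3. Do not add a revised power figure. It would rest on a standard deviation that the article does not give, and the change is only about 1 point.

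The cost is a text correction, or two more patients if the 20% allowance is kept. The design and analysis do not change.

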**Ethics and dissemination:**

This study has been approved by the Ethics Committee of the First Affiliated Hospital of Dalian Medical University (PJ-KS-KY-2021-288). The results of this study will be published via peer-reviewed publications and presentations at conferences.

**Trail registration number:**

ChiCTR2200055793.

STRENGTHS AND LIMITATIONS OF THIS STUDYThis will be the first clinical study to explore the preliminary effects of a family-involvement combined aerobic and resistance exercise protocol on cancer-related fatigue in patients with breast cancer during postoperative chemotherapy.The family members of the intervention group will record activities in a supervision diary and check in a WeChat group throughout the intervention to illustrate the role of the family members in the intervention process.The main limitation of this study will be the small sample size.The findings of this study may only reflect the characteristics of patients in this location given the limited study sites.Another potential limitation is that study protocol lacks a long-term follow-up to assess the ongoing effects of family-involvement exercise.

## Introduction

According to the latest data published for 2020, the number of newly diagnosed cases of breast cancer (BC) in that year reached 2.26 million worldwide and the number of deaths due to BC was 680 000. BC has officially replaced lung cancer as the most common cancer worldwide and ranks first among females as the cause of cancer-related deaths.^1^ In China, approximately 368 000 new BC cases were diagnosed in 2018, and approximately 416 000 new cases of BC were diagnosed in 2020,^2^ showing an increasing trend year by year.^3^ At present, patients with BC in China tend to be younger than those in other populations.^4^ Overall, the number of BC survivors has increased, as the 5-year survival rate of patients with BC has reached 90%. This has been attributed to the progress made in screening, diagnosis and therapeutic strategies applied in BC management.^5^

As a common adjuvant therapy after BC surgery, chemotherapy can improve the survival rate and prolong the survival time of patients with BC.^6 7^ However, patients with low immunity during postoperative chemotherapy are prone to various discomforts, which increase their physical and mental burden and reduce their quality of life. CRF is one of the most common symptoms experienced by patients with BC during postoperative chemotherapy.^8^ According to previous research,^9^ 80%–90% of patients with cancer will experience CRF during treatment, and this condition will persist for a long time. Research has also shown that CRF not only increases the risk of accidental falls in patients with BC but also reduces their tolerance to chemotherapy drugs and increases the incidence of adverse reactions such as nausea and vomiting.^10^ In addition, compared with other symptoms such as pain and depression caused by cancer, CRF has a major negative impact on patients’ social interactions and re-employment.^11^ Studies have shown that CRF in patients is significantly related to muscle strength^12^ and health-related quality of life.^13^ Therefore, it is necessary to improve CRF in patients with BC to promote their return to society and improve their quality of life.

Increased physical activity in patients with BC has been shown to improve CRF.^14^ Physical activity refers to any physical movement that results in energy expenditure caused by skeletal muscle contraction,^15^ including exercise training such as aerobic exercise, resistance exercise, balance exercise and flexibility exercise. Adult patients with BC aged 18–65 years are recommended to engage in regular physical activity at the intensity and for the duration specified by current guidelines.^16^ Aerobic exercise and resistance exercise, as the most common exercise training methods in physical activity, have been proven to be safe and effective.^17^ Studies have found that aerobic exercise combined with resistance exercise has the best effect on improving CRF.^18^

Although the benefits of combined aerobic and resistance exercise for CRF have been proven, many patients with BC do not exercise well. Good external support is one of the important factors for patients’ adherence to exercise.^19^ As an important part of external support for patients, family members are the main facilitators of daily activities and disease care during hospitalisation and after discharge.^20^ Studies have shown that, compared with unsupervised exercise training, supervised exercise training with the participation of family members can better ensure the continuous and regular development of exercise, thereby maintaining and improving exercise effects.^21 22^ In addition, increasing disease-related communication between family members and patients can effectively increase patients’ confidence in treatment, improve the intimacy and adaptability between patients and their family members, and thereby, improve patients’ family functioning.^23^ Therefore, there is an urgent need for a method to promote the active support role of family members in the process of exercise training for patients with BC, which will then enhance the benefits of exercise in improving CRF in these patients.

The current study, therefore, proposes to assess the preliminary effects of a family-involvement exercise protocol on alleviating CRF in patients with BC through a quasi-randomised controlled trial (Q-RCT).

## Methods and materials

### Participant recruitment and eligibility criteria

Patients receiving postoperative chemotherapy for BC in a Grade A tertiary hospital in Dalian will be selected for this study.

The inclusion criteria will be: (1) pathological diagnosis of BC; (2) receiving first course of postoperative chemotherapy for BC; (3) age 18–65 years; (4) able to cooperate actively; (5) voluntary provision of informed consent to participate in this study; and (6) residing with family members during the intervention for 2 months. The exclusion criteria will be: (1) any other serious disease, such as cardiovascular disease, other type of cancer, and so on; (2) exercise contraindications, such as asthma, severe anaemia, disc herniation or other diseases; and (3) mental illness, previous mental illness or family history of mental illness.

One family member will be included for each patient with BC, and the inclusion criteria for family members will be: (1) age >18 years, with primary school education or above, and good communication skills; (2) spouse, parent or child of the patient with BC (immediate family member); (3) main caregiver as determined by the patient with BC and family members for at least 2 months; and (4) voluntary participation in the study. The exclusion criteria will be: (1) payment of remuneration for care of the patient with BC; and (2) a previous history of mental illness.

### Sample size

According to a previous study,^24^ the score for CRF is expected to decrease by 2.29 points. According to the two-sided sample size test formula, a two-sided test with alpha=0.05 and 90% power will require a total sample of 23 patients in each of the two groups. To account for a 20% attrition rate, the required sample size is 56.

### Study design

To avoid contamination among the research participants, this study will adopt a lottery method to randomly divide the hospital’s first and second oncology departments into a control group and intervention group and then select 28 patients from each ward who meet the requirements after screening by the inclusion and exclusion criteria.

The intervention team will consist of a sports rehabilitator, a senior clinical nursing specialist, a head nurse, three responsible nurses and a nursing graduate student. The sports rehabilitator will participate in the formulation of the exercise programme. The nursing specialist will participate in the guidance of the experimental programme. The head nurse and three nurses will be responsible for quality control, identifying problems in the implementation of the programme, and making rectifications. The graduate student will be responsible for explaining the intervention to the patients with BC and their families as well as data collection and collation. Group members will jointly develop an exercise instruction manual (including exercise form, methods, precautions, etc) and record an instructional video for the exercise protocol.

The researcher will explain the purpose and implementation process of the study to the patients with BC when they are admitted to the hospital for their first chemotherapy treatment (T0). After their agreement to participate, participants will be asked to provide written informed consent. The participants will be informed that they can withdraw from the study at any time without any consequences. After obtaining informed consent from the patients, the researcher will conduct the stand-up and sit-down chair test and grip test with patients and issue general information questionnaires along with the R-PFS, FACESⅡ-CV, and FACT-B. The intervention study will begin after the patients (and their family members) have completed their first assessment.

According to previous relevant studies,^25 26^ exercise training begins to play a role in improving CRF during the 8-week exercise intervention process. Therefore, the patients will be tested with the stand-up and sit-down chair test and the grip test at the time of the fourth (T1) and eighth (T2) weekends of the intervention. The exercise completion rates in the two groups will be evaluated at these time points, and the researcher will again issue the general information questionnaires, R-PFS, FACESⅡ-CV and FACT-B to evaluate the effects of the exercise intervention. In the process of distributing the questionnaires, if patients are unable to understand the questionnaire items, the researcher will explain the items. A Consolidated Standards of Reporting Trials flowchart for the study is presented in figure 1. The schedule for trial enrolment, intervention and assessment is presented in table 1.

**Table 1 T1:** Schedule of trial enrolment, intervention and assessment

Study period			
	Beginning of intervention (week 0)	Intervention period (week 4)	End of intervention (week 8)
Inclusion/exclusion criteria	×		
Informed consent	×		
Demographic characteristics	×		
Randomisation and allocation	×		
R-PFS	×	×	×
Stand-up and sit-down chair test	×	×	×
Grip test	×	×	×
Exercise completion rate		×	×
FACESII-CV	×	×	×
FACT-B	×	×	×

FACESⅡ-CV, Family Adaptability and Cohesion Scale, Second Edition-Chinese Version; FACT-B, Functional Assessment of Cancer Therapy-Breast; R-PFS, Piper Fatigue Scale-Revised.

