### Data analysis

Statistical analysis of the results will be completed using SPSS software V.25.0. Analysis of covariance will be applied for comparisons between groups, and paired t-tests will be used for comparisons from before to after exercise within a group. Values of p<0.05 will represent that a significant difference has been detected between test results.

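### With one oncology department per arm, the 90% power and the p<0.05 rule hold only if there is no department effect, a condition the protocol never states

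*Protocol article*

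**What the plan says.** Study design sets the unit of allocation: "this study will adopt a lottery method to randomly divide" the hospital's "first and second oncology departments into a control group and intervention group". The investigators then "select 28 patients from each ward who meet the requirements". The reason given is to avoid contamination between participants. The Abstract gives the same structure: the first department is the intervention arm, and "participants from the second oncology department will be assigned to the control group".

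Sample size takes an expected fall of 2.29 points in the fatigue score from an earlier study and says that "a two-sided test with alpha=0.05 and 90% power will require a total sample of 23 patients in each of the two groups". Attrition of 20% raises this to 56. No SD, ICC, design effect or between-department variance is given.

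Data analysis states: "Analysis of covariance will be applied for comparisons between groups". Significance is declared at p<0.05, and department is not mentioned.

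The Discussion concedes that the study is quasi-randomised rather than a rigorous RCT, that sites are limited and that blinding is impossible. It does not say that treatment cannot be separated from department. The strengths and limitations box names the small sample as the main limitation.

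**The concern.** The lottery makes one draw between two departments, so one unit is allocated to each arm. The sample size and the ANCOVA, as written, treat patients as the independent units. Anything that makes fatigue differ between the departments over the 8 weeks, other than the family component, enters the treatment estimate in full. No analysis of these data can separate the two.

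Two statements are affected. The 90% power and the 5% error rate are correct only when the department effect is zero. A result below p=0.05 on the Piper Fatigue Scale-Revised (R-PFS) would show that the two departments' patients differ, which is not the same as showing that family involvement caused the difference. Naming small sample size as the main limitation also points away from the problem, because recruiting more patients in the same two departments leaves the department component unchanged.

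**Working it through.** **Inputs from the protocol (Sample size):** difference 2.29 points; two-sided alpha 0.05 (z = 1.96); power 90% (z = 1.2816); 23 evaluable per arm; 20% attrition. From Study design: one department per arm.

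**Inputs that are assumptions:** the SD (not stated) and the ICC (not stated; 0.01, 0.02 and 0.05 used for illustration).

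**Step 1: the plan's own figure.** The patient-level formula is n = 2·SD²·(1.96 + 1.2816)²/2.29² per arm. Without an SD, the 23 cannot be reproduced independently, but it can be solved backwards:

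SD = 2.29 / [√(2/23) × 3.2416] = 2.29 / (0.2949 × 3.2416) = 2.396.

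SDs of about 2.34 to 2.40 all round up to 23 (2.29 to 2.34 with the t distribution). So 23 is consistent with a patient-level formula that has no clustering term, provided that 2.29 is a between-group difference. The step to enrolment is 23 × 1.2 = 27.6, hence 28 per arm and 56 in total. The 90% power belongs to the 23 evaluable per arm.

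**Step 2: can department variance be estimated?** With k departments per arm, the between-department degrees of freedom are 2(k − 1). Here k = 1, which gives 0. A department term in the ANCOVA would be identical to the treatment term.

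**Step 3: illustration with m = 23 per arm and SD = 2.396.**

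- SE used by the patient-level test: SD·√(1 − ICC)·√(2/m)
- SE contributed by department: SD·√(2·ICC)
- True SE of the difference: SD·√(2·[ICC + (1 − ICC)/m])
- Type I error of the nominal 5% test: 2·[1 − Φ(1.96 × test SE / true SE)]
- Power with ICC treated as known: Φ(2.29 / true SE − 1.96)

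| ICC | Design effect 1 + 22·ICC | Test SE | Department SE | True SE | Type I error | Power |
|---|---|---|---|---|---|---|
| 0 | 1.00 | 0.706 | 0 | 0.706 | 5.0% | 90% |
| 0.01 | 1.22 | 0.703 | 0.34 | 0.780 | 7.8% | 83% |
| 0.02 | 1.44 | 0.699 | 0.48 | 0.848 | 10.6% | 77% |
| 0.05 | 2.10 | 0.689 | 0.76 | 1.024 | 18.7% | 61% |

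Worked line, ICC 0.05: true SE = 2.396 × √(2 × [0.05 + 0.95/23]) = 2.396 × √0.1826 = 1.024. Type I error: 1.96 × 0.689/1.024 = 1.318, two-sided tail 18.7%. Power: 2.29/1.024 − 1.96 = 0.277, Φ = 61%.

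**Step 4: does a larger sample help?** The department term does not contain m. With 28 per arm instead of 23, the type I error at the same ICCs is 8.4%, 11.8% and 21.3%. It rises, because the test's own SE shrinks while the department component stays.

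**The case against.** The strongest reply is that much of this is disclosed. The study is called quasi-randomised throughout, the aim is limited to preliminary effects, Outcome measurements calls it a pilot, and the Discussion asks for a multicentre RCT. Data analysis says only that p<0.05 marks a detected difference and does not promise proof of efficacy. Allocation by department has a stated reason. Eligibility criteria, hospital, study team, manual and video are common to both arms. This lowers the risk and moderates the claim. It does not supply the missing condition on the power statement, and no section tells the reader that treatment and department are inseparable. Leaving detail to an unseen analysis plan does not help either, since no model can estimate the department variance here.

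Two technical replies also stand. The figures rest on an SD and ICCs that the protocol does not give. And if the ANCOVA adjusts for baseline R-PFS, only the residual department effect after adjustment matters, so the condition is weaker than identical raw fatigue means.

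Some stronger readings are tempting but unsupported:

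- A reader might take the Table 1 row "Randomisation and allocation" as a claim that patients are randomised individually. The row does not say so, and it fits equally well as the point at which a patient's arm is fixed.
- A reader might call the study non-randomised. The departments are allocated by lottery, so one department per arm is the accurate description.
- A reader might conclude that the departments do differ in case mix, treatment or advice. No section says so; the point is that such differences could not be separated from treatment.
- A reader might see randomising patients within each department as the obvious repair. That trades directly against the contamination that Study design sets out to avoid, and the documents do not show it to be the better choice.

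**Conclusion.** The point holds as a defect in the stated power and inference. One department per arm confounds treatment with department completely, and the 90% power for 23 evaluable patients per arm and the 5% error rate are valid only with no department effect on the baseline-adjusted outcome. That conclusion depends on no particular ICC.

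The size is illustrative. For assumed ICCs of 0.01 to 0.05 and an SD of about 2.4, the type I error is about 8% to 19% and power about 83% to 61%. The power figures treat the ICC as known, which this design cannot deliver, so they describe the loss and not an available test. They also assume that 2.29 is a between-group difference, whereas the protocol says only that the score is expected to fall by that amount.

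**What to change.** 1. **Sample size.** State that 90% power for 23 evaluable patients per arm assumes no department effect (ICC = 0). Give the ICC 0.01, 0.02 and 0.05 results as an illustrative sensitivity range, with the SD and ICC labelled as assumptions.
2. **Data analysis and limitations.** Describe the study as a comparison with one department per arm. State that treatment cannot be separated from department, and that p<0.05 will be read as exploratory and not attributed to family involvement alone.
3. **R-PFS ANCOVA.** Adjust for R-PFS at T0 and for key prognostic factors already collected at T0 (age, stage, treatment type). Add that this reduces measured imbalance but does not remove the department effect.

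The cost is a few sentences and a few covariates, with no new data collection. The downside is a less favourable power statement and a weaker claim.
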